### Statistical analyses

The results of all examinations will be expressed as mean ± SD. To clarify the primary endpoint, the changes in the rates of FMD after treatment for 24 months (FMD for 24 months/baseline) will be compared between the RJ and placebo groups using the Student’s *t* test. Non-adherence and missing data will not be used in this analysis. A similar analysis will be performed to compare the changes in FMD at 6, 12, and 18 months between the two groups. For this analysis, missing data will be used according to the period of RJ administration. Other variables and data will be analyzed similarly at 6, 12, 18, and 24 months. There is no plan for any additional analyses. Permitted investigators (KO, YM, TM, KM) will have access to these interim results.

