### Primary endpoint

The primary endpoint is the change in FMD before treatment and 24 months after treatment initiation.

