### Sample size

Unfortunately, there are no reports on changes in FMD due to oral intake of RJ in HD patients. In addition, temporal changes in FMD during HD sessions are unclear. There is general agreement that RJ is a safe food, and our study design poses an extremely low risk to patients as the only other invasive intervention will be the collection of a blood sample (20 ml) every 3 months. Considering these aspects, the proposed sample size was calculated according to the expected agreement rates (60%) of patients, which is the object of this trial. Finally, 135 patients will be enrolled in each of the two groups. For recruitment, the posters that showed purpose, method, risk, and cost are displayed. All authors will obtain written informed consent from potential trial participants or authorized surrogates after oral explanation and providing the explanatory documents. The consent form is original, and it has been approved by our IRB.

We also calculated the proposed sample size according to a previous paper on FMD in HD patients and a meta-analysis of changes in FMD associated with the oral intake of another supplement (magnesium) [30, 31]. In short, 112 patients will be enrolled in each group (a total of 224 patients) with an alpha error rate of 0.05 and a power of 0.8. This is because incomplete data may be available for some patients (approximately 20% of the patients), and patient dropouts may occur before the completion of the trial. Finally, we plan to enroll 135 patients in each group. Regarding such processes, we have had repeated discussions with several biostatisticians. In addition, our decision on sample size was reviewed twice by IRB members, including other biostatisticians. Finally, this policy was approved by IRB because of limited information about the influence of RJ on FMD and the high safety of RJ.

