### FMD measurement

FMD measurements will be performed by professionally trained investigators using the UNEX EF-18VG system (UNEX Corporation, Nagoya, Japan). FMD measurements for the brachial artery will be performed by an experienced cardiologist. Patients’ arms will be immobilized in the extended position, and the brachial artery will be scanned longitudinally 3–5 cm above the antecubital fossa. Baseline measurements for the brachial artery will be recorded, and the cuff will be inflated to 200 mmHg (or 50 mmHg higher than the systolic blood pressure) for 5 min to induce forearm ischemia. Subsequently, the cuff will be deflated, and the diameter of the brachial artery will be measured 60 s after deflation. FMD is defined as the percent change in the diameter of the brachial artery from baseline to post-reactive hyperemia. As a result, FMD will be obtained as a continuous variable. All measurements will be performed by a single investigator who will be blinded to the clinical details.

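### The primary test uses the untransformed ratio of 24-month to baseline FMD, although the endpoint is the change in FMD; the ratio is unstable, and can lose much of the power, if baseline values lie near zero

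*Protocol article*

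**What the plan says.** The section Primary endpoint reads: "The primary endpoint is the change in FMD before treatment and 24 months after treatment initiation". The abstract agrees. Neither says whether the change is absolute (percentage points) or relative.

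The section Statistical analyses makes the endpoint operational as a quotient: "the changes in the rates of FMD after treatment for 24 months (FMD for 24 months/baseline) will be compared", by a two-group Student's t test. It mentions no log transformation, no adjustment for baseline, and no rule for a baseline at or below zero. Missing data are left out of the primary test, and no additional analyses are planned.

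The section FMD measurement states: "FMD is defined as the percent change in the diameter of the brachial artery from baseline to post-reactive hyperemia". The second reading is taken at a fixed time: "the diameter of the brachial artery will be measured 60 s after deflation".

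The section Sample size cites a paper on FMD in hemodialysis patients and "a meta-analysis of changes in FMD associated with the oral intake of another supplement (magnesium"). It arrives at "112 patients will be enrolled in each group (a total of 224 patients") "with an alpha error rate of 0.05 and a power of 0.8". It gives no effect, SD or scale.

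**The concern.** Two things do not fit together.

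**Scale.** A quotient and a difference rank patients differently. A patient going from 1% to 2% and one going from 6% to 12% both have a ratio of 2, but their changes are 1 and 6 percentage points. The article states the endpoint in one form and tests another, without saying which effect the trial is meant to estimate.

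**Denominator.** Baseline FMD is the relative difference between two diameters, the second read at a fixed 60 s and not at its maximum. Nothing keeps it away from zero. A zero baseline has no ratio. If such patients were then treated as missing, those with the poorest dilation would leave the primary comparison. A small positive baseline gives a very large ratio, and a negative baseline reverses the direction.

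At stake are the interpretability of the primary estimate and the relevance of the stated power to the test that will be run.

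**Working it through.** **1. The plan's own figure.** The article gives n = 112 per group, alpha 0.05 and power 0.80, but no effect or SD, so 112 can only be solved backwards. Assuming a two-sided test and equal groups:

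d = (z0.975 + z0.80) × √(2/n) = (1.960 + 0.842) × √(2/112) = 2.802 × 0.1336 = 0.374.

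Forwards, d = 0.375 gives n = 2 × (2.802/0.375)² ≈ 111.6, hence 112. The plan therefore implies a standardized difference of about 0.374 on a scale that it does not name.

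**2. How the ratio behaves (illustrative values).**

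| Baseline FMD | 24-month FMD | Change (points) | Ratio |
|---|---|---|---|
| 5% | 8% | +3 | 1.6 |
| 0.2% | 3.2% | +3 | 16 |
| 0% | 3% | +3 | undefined |
| −1% | 1% | +2 | −1 |
| −1% | −2% | −1 | 2 |

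The same 3-point gain scores 1.6, 16 or nothing. Replacing one ratio of 1.6 by 16 moves the mean of a group of 112 by (16 − 1.6)/112 = 0.13. In the last row a worsening scores as a doubling.

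**3. Power by simulation.** From the article: 112 per group, alpha 0.05, target power 0.80. Assumed, because the article has no such figures: baseline mean 5%, baseline to follow-up correlation 0.5, CV as shown, an additive effect set so that the t test on the change has about 80% power, and normal FMD floored at 0.1%. Each setting has 1,500 simulated trials, so the Monte Carlo error is about 1 percentage point.

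| FMD distribution | CV | Baselines at or below 0.2% | t test on change | t test on ratio | ANCOVA |
|---|---|---|---|---|---|
| Normal | 0.2 | 0.0% | 80.5% | 73.1% | 90.1% |
| Normal | 0.3 | 0.07% | 78.5% | 47.7% | 88.5% |
| Normal | 0.4 | 0.83% | 78.3% | 15.3% | 89.5% |
| Normal | 0.5 | 2.72% | 79.4% | 9.1% | 89.2% |
| Log-normal | 0.3 | 0.0% | 80.5% | 81.6% | 90.6% |
| Log-normal | 0.4 | 0.0% | 79.3% | 84.3% | 89.3% |

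At correlations of 0.5 to 0.6, ANCOVA lies at about 87% to 91% in these settings.

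**4. Wider ranges.**
- Normal FMD, CV 0.2 to 0.6, correlation 0.3 to 0.7: ratio test 8% to 74%, ANCOVA 84% to 95%.
- Log-normal FMD, CV 0.2 to 0.8, additive or multiplicative effect: ratio test 72% to 98%, change score 71% to 81%, ANCOVA 79% to 91%. Here the ratio test sometimes has the most power.
- Normal FMD, mean 4% to 6%, SD 2% to 2.5%: flooring baselines at 0.5% gives the ratio test 37% to 45%, and flooring at 1% gives 52% to 61%.

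**5. Type I error.** With no treatment effect, the ratio test rejects in about 2% to 6% of trials.

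**The case against.** The strongest defence is that the size of the problem depends on data that nobody has shown. If FMD in these patients is right-skewed and stays clear of zero, the ratio test loses little or nothing and may gain. That stands, and it rules out a stronger reading: a reader might infer that the ratio test forfeits most of the planned power, but the article gives no mean, SD, correlation or effect from which this could follow. The log-normal model does exclude values at or below zero by construction, so it marks the favourable end of the range and does not remove the risk.

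Other tempting inferences also lack support.
- A reader might assume that the patients were selected for poor endothelial function, so that baselines near zero are to be expected. The inclusion and exclusion criteria contain no FMD or endothelial criterion, and severe vascular disease needing treatment is excluded.
- A reader might conclude that a different endpoint is being tested. The word change can be read as absolute or relative, so this is an unresolved scale and not proof of a switched endpoint.
- A reader might say that the 80% power has nothing to do with the ratio. The scale behind 112 is not stated, so this cannot be determined either way.

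It is also fair that a randomized comparison without baseline adjustment is inefficient and not wrong, and that rules for awkward values or a transformation may stand in an analysis plan that is not shown. A log-ratio analysis would be steadier: in the normal settings tabulated above its power was 76.7%, 68.5%, 59.2% and 56.0% for CV 0.2 to 0.5, but it still needs a rule for values at or below zero. None of this removes the mismatch, because the article itself fixes both the variable and the test.

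**Conclusion.** The point holds in conditional form. The endpoint is stated as a change, while the primary test is fixed on an untransformed quotient whose denominator can be near zero, zero or negative. The stated power is not shown to apply to that quotient.

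The power loss runs from none to nearly all. Under the assumptions listed it becomes severe with normal FMD at a CV of 0.4 or more, where only about 0.8% of baselines at or below 0.2% already bring the ratio test down to about 15%. ANCOVA varied far less across the same distributions, so the planned test makes the trial depend on a distribution that the article does not document. The damage is to precision and to the meaning of the estimate; the false-positive rate is not raised. Confidence is high on the mismatch and the instability, and low on any single power figure.

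**What to change.** State one scale in both Primary endpoint and Statistical analyses. Suggested text for the latter: FMD at 24 months, in percentage points, will be compared between groups by analysis of covariance with baseline FMD as covariate; the adjusted mean difference with its 95% confidence interval is the primary estimate. Centre may be added as a covariate but is optional, since the Randomization section describes no stratification by centre. Any relative measure should be secondary or descriptive only, preferably on the log scale with a stated rule for values at or below zero.

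In Sample size, give the effect and SD behind 112 per group on that same scale. As the other variables are to be analysed in a similar way, say whether the ratio is meant for them too.

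No new data are needed, because baseline FMD is already measured. The cost is a protocol amendment with IRB approval. Because named investigators have access to interim results, it must be dated before any of them sees comparative data; otherwise the change of primary analysis could look data-driven.

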### Secondary and other endpoints

The secondary and other endpoints are as follows.
FMD at 0, 3, 6, 9, 12, 15, 18, and 21 months after treatment initiation.Aortic calcification index (ACI) at 0, 12, and 24 months after treatment initiation.ESC count in the blood at 0, 3, 6, 9, 12, 15, 18, 21, and 24 months after treatment initiation.Serum levels of vascular endothelial growth factor (VEGF), MCSF, 8-hydroxydeoxyguanosine (OHdG), and malondialdehyde (MDA) at 0, 3, 6, 9, 12, 15, 18, 21, and 24 months after treatment initiation.Incidence of cardiovascular diseases, cerebrovascular diseases, and stenosis of blood access during the 24 months.Adverse events of oral intake of RJ.

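### The only planned primary analysis is an unadjusted t test although baseline FMD is measured; it is valid, but on the change scale usually less precise than a baseline-adjusted model

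*Protocol article*

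**What the plan says.** All places are in the Methods of the protocol article.

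- **Primary endpoint:** "The primary endpoint is the change in FMD before treatment and 24 months after treatment initiation".
- **Secondary and other endpoints:** FMD is scheduled from month 0 ("FMD at 0, 3, 6, 9, 12, 15, 18, and 21 months after treatment initiation"), so a baseline value is planned for every patient.
- **FMD measurement:** "FMD will be obtained as a continuous variable".
- **Statistical analyses:** the variable tested is "FMD for 24 months/baseline", and the changes "will be compared between the RJ and placebo groups" by Student's t test. No covariate is named. The same approach is applied to FMD at 6, 12 and 18 months. The section adds: "There is no plan for any additional analyses".
- **Randomization:** 1:1 from a computerised generator, with no mention of stratification by baseline FMD.
- **Sample size:** 112 per group "with an alpha error rate of 0.05 and a power of 0.8", raised to 135 per group because about 20% of patients may have incomplete data. No effect size, SD or baseline-to-follow-up correlation is given.

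**The concern.** Baseline FMD enters the analysis only as part of the outcome. Subtracting baseline amounts to fixing its coefficient at 1. The coefficient that minimises variance is the regression slope of month-24 FMD on baseline, which for a measure with appreciable within-patient noise is usually below 1. Where it is below 1, change is negatively correlated with baseline, and that predictable part of the variation stays in the error term.

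At stake is precision for which the data will already have been collected. The Sample size section concedes that nothing is known about the effect of royal jelly on FMD in haemodialysis patients and expects about a fifth of the data to be incomplete, so the trial has little precision to spare.

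This is not a detail left to a separate analysis plan. The article names the test and says that nothing further is planned, so an adjusted primary analysis elsewhere would conflict with it.

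**Working it through.** **Inputs from the document:** 112 per group, alpha 0.05, power 0.8, about 20% incomplete data, 135 enrolled per group.

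**Assumptions, not in the document:** two-sided test; planned effect expressed on the change scale; SD0 and SD24 (SDs at baseline and month 24) equal unless stated; correlation rho between baseline and month-24 FMD from 0.3 to 0.9.

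**1. The plan's own figure.** With no effect size or SD stated, 112 cannot be reproduced independently, only inverted. The normal approximation gives d = (1.960 + 0.842) × √(2/112) = 0.374. The t distribution gives d = 0.376, used below.

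**2. Evaluable patients.** 135 × 0.8 = 108 per arm. A t test on change with d = 0.376 then has power 0.785.

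**3. Variance comparison.** Let β be the slope of month-24 on baseline FMD. Then

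Var(change) = residual variance + (1 − β)² × SD0².

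ANCOVA leaves only the residual variance, so it is more precise unless β = 1 (ignoring the one degree of freedom spent).

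With equal SDs, β = rho. The variances in units of SD² are 2(1 − rho) for change and 1 − rho² for ANCOVA, so their ratio is (1 + rho)/2.

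**4. Power at 108 per arm.** The ANCOVA effect is d/√((1 + rho)/2), and the equivalent number per arm is 108 divided by the variance ratio.

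| rho | Variance ratio | Power, t test on change | Power, ANCOVA | Equivalent evaluable per arm |
|---|---|---|---|---|
| 0.3 | 0.65 | 0.785 | 0.927 | 166 |
| 0.5 | 0.75 | 0.785 | 0.888 | 144 |
| 0.7 | 0.85 | 0.785 | 0.847 | 127 |
| 0.9 | 0.95 | 0.785 | 0.806 | 114 |

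Simulation for rho 0.3, 0.5 and 0.7 (4,000 trials each) agreed: 0.786, 0.786 and 0.793 for change; 0.922, 0.883 and 0.843 for ANCOVA.

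**5. Unequal SDs.** Take SD24/SD0 = 1.3 (illustrative) and rho = 0.7. The slope is 0.7 × 1.3 = 0.91. In units of SD0², Var(change) = 1 + 1.69 − 2 × 0.7 × 1.3 = 0.87 and the ANCOVA variance is 1.69 × (1 − 0.49) = 0.862. The ratio is 0.99, and power moves only from 0.785 to 0.789.

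**6. Effect on the raw scale instead.** If 0.376 is in SDs of raw FMD (equal SDs), power for change against ANCOVA is 0.64 against 0.82 (rho 0.3), 0.79 against 0.89 (rho 0.5) and 0.944 against 0.971 (rho 0.7).

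**7. The literal ratio.** Simulation at 108 per arm, with assumed mean FMD 5, SD 2 or 3 and rho 0.3 to 0.7, gave the ratio t test power of 0.31–0.48 with truncated normal FMD and 0.77–0.90 with log-normal FMD. In the log-normal case at rho 0.7 it was 0.84 against 0.83 for raw-scale ANCOVA (SD 2) and 0.90 against 0.82 (SD 3).

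**The case against.** The strongest reply is that the quantified loss belongs to a test that the plan does not literally specify. The Statistical analyses section tests a ratio. Step 7 shows that the power of that ratio can lie far below that of raw-scale ANCOVA, or match or exceed it, depending on an FMD distribution that the document does not give. This stands. A reader might infer that the planned ratio test loses the 2 to 14 percentage points of power in step 4; the documents do not support that. The figures hold for the absolute change named as the primary endpoint.

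The inputs are also uncertain. The scale of the planned effect is not stated, the SDs need not be equal, and rho is unknown. This stands too: steps 5 and 6 show gains from almost nothing to about 18 points.

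A reader might further infer that chance baseline imbalance biases the result, as a second harm beside the lost power. Under the equal-SD assumptions of step 4, a one-standard-error baseline difference at 108 per arm (√(2/108) = 0.136 SD) does shift the unadjusted change by (1 − rho) × 0.136 SD. Against a planned effect of 0.376 × √(2(1 − rho)) SD, that is 21%, 18% and 14% at rho 0.3, 0.5 and 0.7. But under 1:1 randomisation such shifts average to zero, and the standard error of the t test already includes them. They are the same loss of precision, seen conditionally on the imbalance that happens to occur.

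What the reply does not remove is that the plan measures baseline FMD, fixes an analysis that cannot adjust for it, and states that no other analysis is planned.

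**Conclusion.** The point holds as a worthwhile improvement in efficiency. It is not an error of validity: the t test keeps its type I error, and the difference in mean change is unbiased over randomisation.

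On the change scale, baseline adjustment gains precision whenever the slope of month-24 on baseline FMD is not 1. Under the base assumptions (equal SDs, d = 0.376 on the change scale, 108 evaluable per arm), power rises from 0.785 to between 0.93 (rho 0.3) and 0.81 (rho 0.9). The gain is close to zero if the slope is near 1. Because rho, the SDs and the effect scale are not given, the actual gain in this trial cannot be stated, and no direction can be claimed for the literal ratio.

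**What to change.** Before unblinding, replace the primary test with a linear model (ANCOVA) of 24-month FMD on treatment arm, with baseline FMD as covariate. Using the 24-month minus baseline difference as the outcome in the same model gives an identical treatment effect. Report the adjusted mean difference with its 95% confidence interval.

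State the analysed variable on the same absolute-change scale as the Primary endpoint section, in place of the ratio. Keep the unadjusted t test as a supportive analysis, and use the same baseline-adjusted model for FMD at 6, 12 and 18 months.

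The cost is one degree of freedom and no new data, visits or patients. Because the primary variable moves from a relative to an absolute scale, it is more than an editorial change: it needs a protocol modification with IRB approval, as the Study design section provides, and recruitment has already begun.

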## Methods

### Study design

This clinical trial will be conducted in a multicenter, randomized, double-blind, placebo-controlled setting. The study is planned to investigate the superiority of RJ compared to placebo. Three institutions in Japan (Shinzato Clinic Urakami, Maeda Clinic, and Nagasaki Jin Hospital) will participate in this trial. Our RJ is the same as the commercial supplement manufactured in Yamada Bee Farm, and the recommended dosage of this supplement is 3600 mg/day. Therefore, in this trial, HD patients will be divided into two groups: the RJ group, which will be treated with 3600 mg/day of RJ for 24 months, and the placebo group, which will be treated with starch for 24 months. Both RJ and placebo were provided by the Institute for Bee Products and Health Science (Okayama, Japan). The flow chart and timeline of this study are shown in Figs. 1 and 2. The trial has been approved by the certified institutional review board of Nagasaki University Hospital (no. CRB7180001), and the protocol has been registered in the University Hospital Medical Information Network (UMIN000020152) and The Japan Registry of Clinical Trials (jRCTs071200031). In case of protocol modification, the contents of the change will be shown to relevant parties after approval by our IRB. There was no additional collection and use of participant data and biological specimens in ancillary studies. There will be no post-trial care. The individual data will not be disclosed to sponsor, participants, healthcare professionals, the public, and other relevant groups. On the other hand, analyzed data of all participants will be disclosed to all of these groups via publication and public-relation magazine. The full protocol, participant-level dataset, and statistical code will not be disclosed.

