### Randomization

Randomization will be performed by an independent employee of Nagasaki University Hospital using the envelope method, and medical investigators at each institute will be responsible for allocating patients. In short, eligible patients will be randomly assigned in a 1:1 ratio using a computerized random number generator, and the allocation information will be placed in sealed envelopes. Each patient will be assigned a unique number to protect their personal information. The randomized list will be managed by only an independent data manager and will be concealed from all investigators and patients. All information regarding patient selection will remain confidential and unknown to all investigators, including outcome assessors and statisticians, until the completion of the trial. Emergent unblinding will not be possible in this trial.

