### Safety management

If serious adverse events (SAEs) that are speculated to be associated with oral RJ intake, RJ administration will be discontinued. In case of the existence of a causal relation between SAEs and RJ, this study will be terminated. Judgments about RJ-related SAEs will be made by medical investigators at each institute and will be reported to the ethics committee within 24 h and to the coordinate centers within 3–5 days (3 working days). If mild adverse events occur, RJ administration will be discontinued until recovery. In this study, changes in drug dose will not be permitted. On the other hand, RJ administration and all examinations will be terminated in case of participant withdrawal. In addition, the principal investigator (YM) must decide to terminate the trial even if one investigator suggests early termination because of SAEs.

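### The only primary test leaves out non-adherent patients and patients with missing data, so no all-randomised result is planned and the comparison is open to bias

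*Protocol article*

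**What the plan says.** The Study design section of the protocol article sets a superiority aim: "The study is planned to investigate the superiority of RJ compared to placebo". Under Randomization, patients are "randomly assigned in a 1:1 ratio using a computerized random number generator".

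The Statistical analyses section gives one primary test, a Student's t test in which the ratio ("FMD for 24 months/baseline) will be compared between the RJ and placebo groups") is the outcome. It then restricts who enters: "Non-adherence and missing data will not be used in this analysis". A different rule covers the comparisons at 6, 12 and 18 months: "For this analysis, missing data will be used according to the period of RJ administration". The section also says: "There is no plan for any additional analyses".

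Three other sections bear on who is lost:
- **Sample size** expects roughly 20% of patients to have incomplete data and mentions dropout.
- **Safety management** says "If mild adverse events occur, RJ administration will be discontinued until recovery", and ends all examinations when a participant withdraws.
- **Data collection and management** has outcome data recorded at the time of the event for patients who discontinue or deviate. No analysis is said to use those data.

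The article mentions no all-randomised analysis set, no imputation, no likelihood-based model and no sensitivity analysis.

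**The concern.** Randomisation makes the two groups comparable at the start. A rule that selects patients on what happens afterwards (whether they kept taking the product, whether they reached the 24-month measurement) can undo that. If the reasons for leaving differ between arms, or relate differently to endothelial function, the t test compares groups that are no longer the randomised ones. It can neither detect nor correct this.

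The article fixes the exclusion as a rule; it is not detail left to an analysis plan. No other planned analysis would show a reader whether the result depends on it. Because the article gives no definition of non-adherence, it also leaves open who is dropped.

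**Working it through.** **The plan's own figures.** Sample size gives 112 per group "with an alpha error rate of 0.05 and a power of 0.8", then 135 per group after an allowance of about 20%.
- 112 × 1.20 = 134.4, rounded up to 135, which reproduces the enrolled number.
- Expected loss at 20%: 0.20 × 135 = 27 per arm (54 of 270), leaving 108 per arm.
- The allowance is worded for incomplete data and dropout. Non-adherent patients with complete data come on top.

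**Implied effect.** The article states no effect size, SD or sidedness. Assuming a two-sided test and the normal approximation, effect/SD = (1.960 + 0.842) × √(2/112) = 0.374. The t-based value is 0.376. A one-sided test would imply 0.332.

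**Bias formula.** Let a fraction f be excluded in each arm, and let D be the RJ-minus-placebo difference. The all-randomised difference is (1 − f) × D(retained) + f × D(excluded), so

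bias = D(retained) − D(all) = f × [D(retained) − D(excluded)].

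The difference among the excluded is not enough on its own:
- If the true effect were 0.5 SD in everyone, the excluded arms would differ by 0.5 SD and the bias would be zero.
- If the all-randomised effect is zero, f = 0.20 and the excluded differ by −0.5 SD, the retained differ by 0.20 × 0.5 / 0.80 = +0.125 SD. The bias is then 0.20 × (0.125 + 0.5) = 0.125 SD.

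With unequal fractions, write g for the retained-minus-excluded mean within an arm. Then bias = f(RJ) × g(RJ) − f(placebo) × g(placebo), which reduces to the formula above when the fractions are equal.

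**Scenarios with no true effect.** There are 135 randomised per arm and a two-sided 5% test. The standard error is √(1/n(RJ) + 1/n(placebo)) in SD units, where n is the number retained. All exclusion rates and gaps are assumptions; the article gives only the overall figure of about 20%.

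| Excluded, RJ / placebo | g, RJ / placebo (SD) | Bias (SD) | Type I error |
|---|---|---|---|
| 20% / 20% | 0.5 / 0.5 | 0 | 5.0% |
| 25% / 15% | 0.5 / 0.5 | 0.05 | 6.6% |
| 25% / 15% | 1.0 / 1.0 | 0.10 | 11.4% |
| 20% / 20% | 0.5 / 0 | 0.10 | 11.4% |
| 30% / 10% | 0.5 / 0.5 | 0.10 | 11.3% |
| 30% / 10% | 1.0 / 1.0 | 0.20 | 30.8% |

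Worked example, third row: bias = 0.25 × 1 − 0.15 × 1 = 0.10. The standard error is √(1/101.25 + 1/114.75) = 0.136, and 0.10/0.136 = 0.73. The rejection probability is P(Z > 1.96 − 0.73) + P(Z < −1.96 − 0.73) ≈ 0.110 + 0.004 = 0.114. Relative to the design effect, 0.10/0.376 = 27%. Swapping the arms gives a bias of the same size against RJ.

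**Power.** At 0.374 SD, 108 completers per arm give 78.6%. All 135 per arm give 86.8% with the full effect, and 83.2%, 79.1% or 69.2% if non-adherence dilutes it by an assumed 5%, 10% or 20%. The figures for 135 are upper limits, since some month-24 values will be missing.

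**The case against.** The strongest defence is blinding. Adherence judgements and pauses for adverse events are made without knowledge of the arm, and emergency unblinding is not possible. If exclusions are balanced and equally related to outcome, the bias is zero, as the first row of the table shows. This stands as a reason to expect less bias, but the product itself can still cause different rates of intolerance or stopping under perfect blinding. It could also be said that the sentence ruling out additional analyses was meant only for subgroup or adjusted analyses. Even so, the article states no all-randomised analysis.

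A reader might infer four stronger things that the documents do not support:
- **Patients with hospitalisation or vascular events are removed.** The rule names only non-adherence and missing data. Vascular events are a planned endpoint, and such a patient who stays on product and has a 24-month FMD remains in the test. The eligibility criteria on expected survival and severe vascular disease also limit this route.
- **A pause for a mild adverse event counts as non-adherence.** The article does not say so. Without a definition, it is only a possibility.
- **The rule at 6, 12 and 18 months applies to the RJ arm alone.** The article uses RJ administration loosely for blinded product, for instance when describing participant withdrawal. The wording is unclear, but an arm-specific rule is not established.
- **The result will favour RJ.** Nothing in the documents fixes the direction.

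**Conclusion.** The point holds in this form: the sole primary test of a superiority trial excludes patients on post-randomisation grounds, one of those grounds is undefined in the article, and no all-randomised or sensitivity analysis is planned. With about 27 of 135 patients per arm expected to have incomplete data, plus non-adherent patients with complete data, the exclusions are too many to ignore.

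Bias is possible, not established. Under the assumed scenarios it runs from none (type I error 5%) to about 0.10 SD (about 11%) with moderate imbalance, and further only under more extreme assumptions. The 27% comparison also assumes a two-sided test. The case for change does not depend on any one scenario: the plan gives no means of telling which of them occurred.

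**What to change.** Replace the exclusion rule with a primary analysis of all randomised patients as assigned, regardless of adherence, using every FMD value collected from 0 to 24 months. One suitable choice is a repeated-measures mixed model with baseline FMD, visit, treatment and treatment-by-visit, with the month-24 contrast as the primary estimate. State openly that this replaces the 24-month/baseline ratio; if the ratio is kept, apply the same population rule to it.

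In addition:
- Add a sensitivity analysis in which missing values are assumed worse than predicted (missing not at random).
- Keep the adherent-completer t test as a labelled supportive analysis, with adherence defined before unblinding.
- Apply one missing-data rule to both arms at all visits, including 6, 12 and 18 months.

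The cost is an amendment before unblinding and a little more analysis; the FMD visits are already scheduled every 3 months. The estimate may be diluted by non-adherence. Patients whose examinations end at withdrawal contribute only the values collected up to then, so the model relies on an assumption about their later values, which the sensitivity analysis is there to test.
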